## Methods

### Design

This is a multi-centre two-arm pilot RCT exploring the feasibility and potential effectiveness of CBT for relatives of missing persons suffering from psychopathology, in comparison with a waiting list control group. The intervention group will start with the treatment within 1 week after randomisation. The waiting list control group will receive the treatment 12 weeks after randomisation. An allocation ratio of 1:1 will be used. The participants will be asked to fill in questionnaires prior to the treatment and 1, 12, and 24 weeks post-treatment. Participants in the waiting list control group will complete an additional questionnaire 1 week prior to their actual start of the treatment. In addition, the participant will be asked to complete a brief questionnaire at the start of each session to assess the potential change in repetitive negative thinking, intrusive memories, and self-compassion during the treatment.

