#### Other measures

Sociodemographic variables (e.g., gender, date of birth, and educational level) of the participants and missing persons will be registered at the first measurement occasion. The number of sessions the participants attended will be registered at the 1-week post-treatment assessment. In case the participant attended less than eight sessions, the reason(s) for drop-out will be registered. The following two open-ended questions regarding the evaluation of the treatment will also be administered at the 1-week post-treatment assessment: “About which aspects of the treatment are you satisfied?” and “About which aspects of the treatment are you less satisfied?”. The questionnaires and time points are summarised in Table 1.

**Table 1 Tab1:** Overview of variables, concepts, measures, and time points

Variable	Concept	Measure	Time points
Primary outcome measures	Severity of PCBD symptoms	ICG	T0, T0.1, T1, FU1, FU2
Secondary outcome measures	Severity of PTSD symptoms	PCL-5	T0, T0.1, T1, FU1, FU2
	Severity of depressive symptoms	IDS-SR	T0, T0.1, T1, FU1, FU2
	Extent of mindfulness	SMQ	T0, T0.1, T1, FU1, FU2
Mediator	Severity of grief cognitions	GCQ	T0, T0.1, T1, FU1, FU2
	Severity of rumination	RRS	T0, T0.1, T1, FU1, FU2
	Severity of repetitive negative thinking	PTQ	T0, T0.1, T1, FU1, FU2
	Ability to be self-compassionate	SCS	T0, T0.1, T1, FU1, FU2
	Severity of intrusive memories	TMQ	T0, T0.1, T1, FU1, FU2
	Severity of avoidance behaviour	DAAPGQ	T0, T0.1, T1, FU1, FU2
Process of change session by session	Ability to be self-compassionate	SCS-SF	Start of each treatment session
	Severity of intrusive memories and images	Intrusive memories and images vas	Start of each treatment session
	Frequency of repetitive negative thinking	RNT vas	Start of each treatment session
Other variables	Sociodemographic information		T0
	Evaluation of the treatment and reason(s) for drop-out		T1

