#### Treatment

The treatment is manualized and consists of eight 45-min individual face-to-face therapy sessions offered in a period of maximally 12 weeks. The treatment protocol draws from CBT for treatment of PCBD [23, 69]. Participants learn cognitive behavioural skills and mindfulness practices that enable them to disengage from dysfunctional cognitive patterns related to their missing loved one, both during the sessions and through homework assignments.

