##### Data analyses

Within-subjects repeated measures ANOVA with time (baseline, 1, 12, and 24 weeks post-treatment) as the repeated measure will be performed to evaluate the effects of the treatment in terms of changes in mean scores of PCBD.

Between-subjects multivariate analysis of covariance (MANCOVA) will be performed to compare changes in PCBD, MDD, PTSDD, and mindfulness scores between the treatment and waiting list condition. Specifically, scores at post-treatment (in the treatment condition) and post-waiting period (in the waiting list condition) on measures tapping these phenomena will be compared, including baseline scores as covariates.

Within-subjects MANCOVA with time (baseline, 1, 12, and 24 weeks post-treatment) as the repeated measure will be performed to evaluate the short- and long-term effects of the treatment in terms of change in mean scores of PCBD, MDD, PTSD, and mindfulness. To test whether the treatment effect is mediated by changes in cognitive variables (i.e., grief cognitions, intrusive memories, rumination, and repetitive negative thinking), behavioural variables (i.e., avoidance behaviour), and self-compassion, only the scores of measures tapping these constructs that show the strongest association (based on univariate analyses) will be added to a multiple regression model. Finally, to assess the potential change at micro-level in repetitive negative thinking, intrusive memories and self-compassion throughout the course of the treatment a within-subjects repeated measures ANOVA with time (session 1 to session 8) as the repeated measure will be performed with mean scores of measures tapping repetitive negative thinking, intrusive memories, and self-compassion as outcome measures.

Data will be analysed according to the intention-to-treat principle. Missing data will be handled using multiple imputations. The Statistical Package for the Social Sciences will be used for the analysis. The small sample size of the pilot RCT increases the risk of type II error; the preliminary results regarding the potential effectiveness will therefore be reported with caution following the recommendations for conducting a pilot study [78].

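### The waiting-list outcome T0.1 is timed from each participant's actual start of treatment, so it has no due date for non-starters and falls late for delayed starters; T1 has a similar gap

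*Protocol article*

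**What the plan says.** The protocol article's Design section sets the start of treatment in each arm. For CBT: "The intervention group will start with the treatment within 1 week after randomisation". For the waiting list: "The waiting list control group will receive the treatment 12 weeks after randomisation".

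The assessments are then timed from treatment, not from randomisation. For all participants: "The participants will be asked to fill in questionnaires prior to the treatment and 1, 12, and 24 weeks post-treatment". For the control arm: "Participants in the waiting list control group will complete an additional questionnaire 1 week prior to their actual start of the treatment". This extra assessment is T0.1 in Table 1, whose footnote calls it the post-waiting period measure.

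In the between-arm analysis (Data analyses), "scores at post-treatment (in the treatment condition) and post-waiting period (in the waiting list condition) on measures tapping these phenomena will be compared", with baseline scores as covariates. Study objectives lists this comparison as secondary; the primary analysis is within-group.

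On incomplete data the same section says: "Data will be analysed according to the intention-to-treat principle. Missing data will be handled using multiple imputations". Other measures records the number of sessions attended at the 1-week post-treatment assessment and adds: "In case the participant attended less than eight sessions, the reason(s) for drop-out will be registered".

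**The concern.** The randomised comparison needs an outcome from everyone randomised, at a time that does not depend on what happened to them afterwards. T0.1 is the control arm's only outcome in that comparison, and its single timing rule counts back from an event that some participants may never reach. A person who declines treatment after waiting, or leaves during the wait, has no start date and so no due date for T0.1. A person whose start slips gets T0.1 later.

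Non-start is realistic here. The Discussion says that recruitment is aimed at people who are not seeking treatment, and the waiting list asks them to still want it about 12 weeks after randomisation. Whether they do may be related to how their symptoms changed in that time. If so, the available T0.1 scores come from a selected part of the arm. What is at stake is the only randomised evidence in the trial, which is meant to inform a larger RCT.

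**Working it through.** **1. The schedule as planned.** Inputs from Design and Treatment: waiting-list start at week 12; CBT start within 1 week; "eight 45-min individual face-to-face therapy sessions offered in a period of maximally 12 weeks"; T1 at 1 week after treatment.

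- T0.1 on schedule: 12 − 1 = week 11 after randomisation.
- T1 at the latest: 1 + 12 + 1 = week 14.

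**2. The schedule when treatment does not go to plan.**

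| Situation | Assessment | Due date as written |
|---|---|---|
| Waiting list, start delayed by d weeks | T0.1 | week 11 + d |
| Waiting list, never starts | T0.1 | none |
| CBT arm, never starts | T1 | none |
| CBT arm, stops early | T1 | apparently assessed (Other measures), but no date counted from randomisation |

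The gap for non-starters is therefore in both arms. The difference between the arms is narrower: for T1 there is text suggesting that partial attenders are assessed, and for T0.1 there is no similar text.

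**3. What imputation has to work with.** Table 1 lists the outcome and mediator questionnaires at T0, T0.1, T1, FU1 and FU2, and the session measures at the start of each treatment session. A waiting-list participant who never starts has no sessions, so nothing is recorded between T0 and T0.1. If T0.1 is missing, it can be imputed only from baseline data and from the pattern among those who have T0.1. That handles non-start explained by baseline. It does not handle non-start that depends on change during the wait.

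**4. An illustration of size.** The documents give no rate of non-start and no difference between starters and non-starters, so every input here is an assumption. For a complete-case mean,

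shift = (share missing) × (difference between starters and non-starters, in SD).

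- Applying the plan's 19% drop-out to the wait: 0.19 × 15 = 2.85, about 3 of 15. With a difference of 0.5 to 1 SD: 3/15 × 0.5 = 0.10 SD to 3/15 × 1.0 = 0.20 SD.
- Wider range: 1/15 × 0.5 = 0.03 SD to 5/15 × 1.0 = 0.33 SD.

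The 19% comes from a review of CBT studies (Sample size), not from waiting periods. The planned analysis adjusts for baseline and imputes, so the part of the difference that baseline explains would drop out. If baseline explained half of a 0.20 SD shift, 0.20 × (1 − 0.5) = 0.10 SD would remain; if it explained all of it, none would.

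**5. Direction.** If those who do not start have improved, the waiting-list mean is too severe and CBT looks better. If they are worse, for example because they sought care elsewhere, the shift goes against CBT. Nothing in the document settles which.

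**The case against.** The strongest case on the other side has five parts.

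- **The start is scheduled.** With treatment due at week 12, T0.1 has a nominal date known at randomisation. The rule covers waiting-list participants without exception, and no text withholds T0.1 from people who decline. This stands: a reader might infer that non-starters have no control outcome, but the document does not say so. What it lacks is a date for them. The post-waiting label does not supply one, and the operative rule names the actual start.
- **T1 is also tied to treatment.** A reader might infer that selection affects one arm only. That is not supported. The text on fewer than eight sessions is not arm-specific and could include zero sessions.
- **Intention to treat with multiple imputation is planned.** Participants without T0.1 therefore stay in the comparison, and the SD figures describe an analysis that is not planned. Both points are correct. They do not remove the problem, because imputation has no information from the wait.
- **The imputation model is not described.** A reader might infer that never-starters would be given post-treatment scores as if treated successfully, or that the CBT effect is inflated. Both rest on details that an article commonly leaves to the full protocol or SAP, and the direction is open.
- **The comparison is secondary, in a pilot of 15 per arm.** The plan promises to report effectiveness with caution. This limits the consequence. It is still the only randomised contrast.

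**Conclusion.** The concern holds in a limited form. The protocol times the only control outcome of its randomised comparison from a post-randomisation event, although its own schedule implies a fixed week. Read as written, waiting-list non-starters have no due date for T0.1 and delayed starters are measured late. CBT-arm non-starters have no due date for T1 either. If T0.1 is lost for reasons linked to change during the wait, baseline-only imputation cannot correct it.

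The size and direction of any bias are unknown. The 0.03 to 0.33 SD range is a complete-case illustration that rests on assumed numbers of non-starters and an assumed difference from starters; it is not an estimate of bias in the planned analysis. The point is worth correcting because the comparison is the trial's only randomised evidence and the remedy is cheap.

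**What to change.** In Design, replace the T0.1 trigger with a fixed time from randomisation: every waiting-list participant receives T0.1 at week 11, the week the schedule already implies, whether treatment starts on time, is delayed, is declined or never starts. Collection ends only if the participant withdraws consent to questionnaires.

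In the same place, give T1 a matching fallback date counted from randomisation for CBT-arm participants who never start or who stop early, so that both arms have a defined outcome time for everyone randomised.

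Keep the intention-to-treat set as stated in Data analyses. A within-group analysis that does not impute post-treatment scores for people who never started departs from that principle, so it should appear only as a declared sensitivity analysis.

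The cost is a few sentences of rewording and some reminders to people who have declined treatment. The T0.1 questionnaire is already planned for the whole waiting-list arm, and no treatment procedure changes.

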### Ethics approval

Ethics approval for performing this study has been obtained from the Ethical Committee Psychology at the University of Groningen in the Netherlands (ppo-014-087).

### Participants

First, second, and third degree (adoption- or step-) family members, spouses, and friends of missing persons, who are missing for more than 3 months, are fluent in written and spoken Dutch, and are 18 years of age or older are eligible to sign up for the study. A missing person is defined as “Anyone whose whereabouts is unknown whatever the circumstances of disappearance. They will be considered missing until located and their well-being or otherwise established” (p. 15) [39]. The 3-month criterion was used in a previous study [40] and is also chosen for this study in consultation with representatives of a peer support group and a non-governmental organisation for relatives of missing persons in the Netherlands. Additional inclusion criteria are (1) meeting criteria for PCBD, MDD, and/or PTSD, (2) written informed consent, (3) absence of mental retardation, (4) absence of substance abuse or dependence, (5) absence of psychotic disorder, (6) no high risk of suicide, and (7) no concurrent psychological treatment. In case the missing loved one will be found dead or alive during the period of participation, the participant is offered the opportunity to finish the treatment but will be excluded from further analyses.

### Recruitment of participants

All recruitment procedures aim to enrol individuals of whom a loved one has been missing for participation in a survey study. The survey study aims to explore the psychological consequences for relatives of missing persons. The survey study and pilot RCT are both part of the same research project. We will recruit participants through several pathways. Firstly, representatives from a television show focused on the search of missing persons and a peer support group will distribute invitation letters to relatives of missing persons. Secondly, Victim Support the Netherlands, a governmental organisation in which professionals, mostly social workers, offer practical and legal support to victims, will inform potential participants about the research project. Thirdly, other participants will be recruited via announcements in the media, presentations at meetings for relatives of missing persons, and snowball sampling (each participant is asked to invite others). After signing up for the survey study, the participants will be sent a questionnaire including an information letter and informed consent form for participation in the survey study. The letter informs participants about the aims of the survey study and the possibility to participate in a subsequent study designed to evaluate a psychological intervention specifically developed for relatives of missing persons.

### Procedure and randomisation

After receiving the completed questionnaires and the signed informed consent form for participation in the survey study, the participants will be screened for in- and exclusion criteria for the intervention study. The screening procedure comprises two parts. The first part consists of screening participants for in- and exclusion criteria based on questionnaires (questionnaires and cut-off criteria are described below). Participants who score above the threshold for PCBD, MDD, and/or PTSD will be offered written information about the intervention study together with an informed consent form for participation in the intervention study. The second part of the screening procedure consists of a clinical interview composed of the M.I.N.I. Plus version 5.0.0. and the Traumatic Grief Interview. A trained independent psychologist will conduct the interview by telephone. The M.I.N.I. Plus is developed to diagnose axis I DSM-IV psychiatric disorders and has good psychometric properties [41, 42]. The following modules of the M.I.N.I. Plus will be used: major depressive episode, dysthymia, suicidality, PTSD, alcoholic dependence, substance dependence, and psychotic disorders. In addition, the Traumatic Grief Interview will be administered to assess symptoms of PCBD [43]; based on this interview, participants meet criteria for PCBD when they score a 2 (“sometimes”) or higher on at least 1 B-cluster symptom, at least 6 C-cluster symptoms and a score of 1 (“seldom”) or higher on the D-cluster symptom in accord with the proposed criteria of PCBD in the DSM-5 with exclusion of the criterion that at least 12 months must have been elapsed since the loved one has gone missing [14].

Randomisation will take place after the participant is screened for eligibility based on the M.I.N.I. Plus and the TGI. A random number generator will be used to perform the blocking randomisation procedure. Relatives of the same missing person will be allocated to the same study arm (i.e., intervention or waiting list condition), in order to prevent transfer of information. An independent researcher will conduct the randomisation procedure. Neither the participants nor the researchers will be blinded. The M.I.N.I. Plus and the Traumatic Grief Interview will be conducted again after the treatment, to examine whether numbers of cases of PCBD, MDD, and PTSD have decreased. The researchers will reimburse costs related to the treatment that are not covered by the respondents’ health insurance. Travel expenses that are related to the visits to the therapist will also be reimbursed (see Fig. 1 for a flowchart of the procedures).

**Fig. 1 Fig1:**
[figure not shown]
Schematic display of the study procedures

### Sample size

To find a within-subjects difference in PCBD symptom across four time points (baseline and 1, 12, and 24 weeks post-treatment) of medium effect size [19] with a power of 80 %, an *α* of 0.05, assuming the correlation between the measures to be 0.50, a sample size of in total 24 participants is sufficient. By taking into account a drop-out rate of 19 %, based on a review that reported a mean attrition rate of 19 % among studies that evaluated the effectiveness of CBT for bereavement-related psychopathology [19], a total sample size of 29 is required.

### Measures

#### Primary outcome measure

##### Inventory of complicated grief

Self-rated symptoms of complicated grief as underlying concept of PCBD will be assessed with the 19-item Inventory of Complicated Grief [44, 45]. Respondents are asked to rate how frequently they experienced 19 grief reactions during the last month, on a 5-point scale ranging from 0 (“never”) to 4 (“always”). The Inventory of Complicated Grief is together with the PG-13 [46] a frequently used instrument to administer grief reactions. Opposed to the former instrument, a validated Dutch translation of the PG-13 is not available. The Dutch translation of the Inventory of Complicated Grief, that demonstrated adequate psychometric properties [45], is therefore chosen as primary outcome measure. We adapted the items of the Inventory of Complicated Grief by referring to the disappearance instead of death (e.g., “Ever since he/she has been missing it is hard for me to trust people”). The Inventory of Complicated Grief is also used as screening instrument in the first part of the screening procedure (see Fig. 1) to assess whether the participant is eligible for the treatment. Participants meet the criteria for PCBD when they score above the cut-off of >25 [44].

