### Study objectives

The aim of this pilot study is to evaluate the feasibility and the potential effectiveness of CBT with elements of mindfulness in reducing PCBD, MDD, and PTSD symptoms and enhancing the extent of mindfulness among relatives of missing persons. Based on previous studies, we expect that the treatment effect will be mediated by changes in negative cognitive and behavioural variables plus enhancement of self-compassion.

The feasibility of the pilot RCT will be explored by the evaluation of the (1) specifics of potential participation bias, (2) attrition rate, (3) methods used and study design, (4) treatment fidelity, and (5) strengths and suggestions for improvements of the treatment from the perspective of the participant. The primary objective of the analysis of the pilot RCT is to assess changes in mean scores on a measure of PCBD from baseline to 1, 12, and 24 weeks post-treatment. A within-group instead of a between-groups analysis will be executed because this will give the most rigorous information about the potential effects of this treatment given the small sample size.

Secondary objectives of the analysis of the pilot RCT are (1) to evaluate whether the mean scores on measures tapping PCBD, MDD, PTSD, and mindfulness of the treatment group differ from the waiting list control group at the post-treatment/post-waiting period assessment when adjusting for the baseline scores and (2) to test whether the treatment effect is mediated by changes in negative cognitive variables (i.e., reductions in negative grief cognitions, intrusive memories, rumination, and repetitive negative thinking) and behavioural variables (i.e., avoidance behaviours) and enhancement of self-compassion. In addition, the extent of change in repetitive negative thinking, intrusive memories, and self-compassion in response to the treatment will be explored at micro-level by means of tracking measures tapping these constructs during the treatment.

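### The article appears to use the screening survey's grief score as the primary baseline, so the within-group result would include some regression to the mean

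*Protocol article*

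**What the plan says.** **Screening.** Under Procedure and randomisation: "After receiving the completed questionnaires and the signed informed consent form for participation in the survey study, the participants will be screened". Those above the threshold for grief, depression and/or PTSD receive information on the trial. Consent and a telephone interview (M.I.N.I. Plus and Traumatic Grief Interview) follow, then randomisation. Of the primary outcome the article says: "The Inventory of Complicated Grief is also used as screening instrument in the first part of the screening procedure". The PCL-5 and IDS-SR have the same double role. The cut-offs are ICG above 25, PCL-5 above 38 or a diagnostic rule, and IDS-SR above 13.

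**Timing of T0.** Table 1 gives every outcome at T0, T0.1, T1 and two follow-ups, with no screening occasion. Its footnote calls T0 only the baseline measure. Under Other measures, sociodemographic data "will be registered at the first measurement occasion", and Table 1 places them at T0. The Design section says only that questionnaires are completed before treatment. It then adds: "Participants in the waiting list control group will complete an additional questionnaire 1 week prior to their actual start of the treatment". No second pre-treatment measure is described for the CBT arm. That arm starts treatment within 1 week of randomisation. No maximum interval from survey to randomisation is given.

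**Primary analysis.** Study objectives: "A within-group instead of a between-groups analysis will be executed". Data analyses: "Within-subjects repeated measures ANOVA with time (baseline, 1, 12, and 24 weeks post-treatment) as the repeated measure will be performed".

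**The concern.** A score that helped a person pass a cut-off is, on average, partly high by chance, and it falls on re-measurement without any treatment. If the screening ICG is also the baseline, that fall sits inside the quantity the primary analysis tests. So does any change during the mailed information, consent, interview and randomisation steps before session 1. A one-group analysis over time cannot separate either from the effect of therapy.

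This differs from the lack of a control in the primary analysis. It concerns where the baseline score comes from, and for the within-group estimate it can be repaired on its own.

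**Working it through.** **1. Is T0 the survey?** Four places point that way.
- Screening uses the completed survey questionnaires, and only interviews are described between then and randomisation.
- Table 1 has no occasion for screening scores other than T0.
- Sociodemographic data belong to the first measurement occasion, which Table 1 labels T0.
- Feasibility analyses will compare volunteers with refusers on sociodemographic data and on mean grief, depression and PTSD scores. If refusers are people who declined the trial after the survey, those data can only come from the survey.

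This is inference. None of these passages states it.

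**2. The plan's own figure.** The sample size is for a difference "of medium effect size [19] with a power of 80" per cent, four time points, α = 0.05 and correlation 0.50. The numerical effect size is not given; I take f = 0.25. With λ = n·m·f²/(1−ρ), n = 24 gives 24 × 4 × 0.0625 / 0.50 = 12, on 3 and 69 degrees of freedom. Power is 81.7% (79.7% at n = 23), so 24 is reproduced. The stated 29 is 24 × 1.19 = 28.6, rounded up; 24/0.81 = 29.6 would give 30, the number in the abstract.

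For one high baseline and three equal later means, f = d·√3/4. So d = 0.25 × 4/√3 = 0.58 SD. This is the yardstick.

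**3. Upper bound: entry on the ICG alone.** Expected fall in survey-population SD = (1−r) · φ(c)/(1−Φ(c)), where r is the retest correlation and c the standardised cut-off. The share of survey respondents above the cut-off is assumed.

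| Share above cut-off | φ(c)/(1−Φ(c)) | Fall, r = 0.50 | Fall, r = 0.80 |
|---|---|---|---|
| 70% | 0.50 | 0.25 | 0.10 |
| 50% | 0.80 | 0.40 | 0.16 |
| 30% | 1.16 | 0.58 | 0.23 |

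This is not the article's entry rule.

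**4. The article's rule: any of three instruments, then an interview.** I rely on a simulation with no treatment effect, n = 24 and the planned repeated-measures ANOVA. Assumed inputs: true scores correlated 0.7 across instruments, and 30% or 50% above each cut-off. The lower end of each range includes the interview.

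| Same-day errors across instruments | r | Spurious fall (SD) | False positives |
|---|---|---|---|
| Correlated 0.7 | 0.50 | 0.17–0.36 | 12–40% |
| Correlated 0.7 | 0.70 | 0.09–0.22 | 8–24% |
| Correlated 0.7 | 0.80 | 0.06–0.15 | 7–19% |
| Independent | 0.50 | 0.06–0.14 | 6–9% |
| Independent | 0.80 | 0.02–0.06 | 5–6% |

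At r = 0.90 with independent errors, 50% above each cut-off and the interview, the fall is 0.01 SD and the false-positive rate about 5%. With a fresh ICG taken after selection, the expected change is 0 and the false-positive rate 4–6%.

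**5. Which r?** The protocol's 0.50 refers to repeated measures in enrolled people, whose scores are range-restricted. For ICG-only entry cut at the mean, the variance ratio among those selected is 1 − 2/π = 0.363. Then 0.50 among the selected corresponds to r² = 0.25/(0.75 × 0.363 + 0.25) = 0.478, so r = 0.69 unselected. The fall becomes (1 − 0.69) × 0.80 ≈ 0.25 SD, not 0.40. The same correction, weaker in size, applies to the three-instrument rule, so the r = 0.50 rows in step 4 are an upper end.

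**The case against.** The strongest reply is that the premise is not in the text. A pre-treatment questionnaire could be a separate assessment, and the first measurement occasion could mean the first in the trial. The survey's contents are not listed, so nothing shows that it carried the mindfulness and mediator scales that Table 1 places at T0. The missing figure might settle it. That stands: a reader might infer that the article declares the survey to be T0, and it does not.

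Other stronger readings also fail.
- **A baseline chosen for being high.** This is only partly true of the ICG. A person can enter with an ICG of 25 or below through the PCL-5 or IDS-SR.
- **An unlimited gap before treatment.** The article states no maximum from survey to randomisation, which a condensed article may leave out. It does cap randomisation to treatment at 1 week in the CBT arm.
- **A spurious fall of 0.40 SD.** That needs ICG-only entry and treats the protocol's 0.50 as an unselected retest correlation. It lies above the whole range under the actual rule.
- **Bias in the randomised comparison.** Both arms pass through the same selection, and baseline covariates are planned. An old baseline may adjust less well, but that is lost precision.

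The article also promises cautious reporting as a pilot. It ties that caution to type II error, whereas this problem inflates the apparent effect.

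**Conclusion.** The point holds in limited form. As described, the screening ICG appears to double as T0. If so, the within-group primary result includes regression to the mean and any change between survey and session 1. Under the article's entry rule the regression part is about 0.01 to 0.36 SD, with a false-positive rate of about 5% to 40%, against about 0.58 SD for the planned effect if f = 0.25.

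The range rests on the assumed shares above the cut-offs, retest correlations and error correlations. The low end is negligible. The high end needs r = 0.50 in unselected respondents and strongly correlated same-day errors. The two SD units are also not identical: the fall is in survey-population SD, the planned effect in SD of the analysed group. Change over the interval itself is not quantified, because the interval is not stated.

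**What to change.** Use the survey scores for screening only. Repeat at least the 19-item ICG after the eligibility interview and before randomisation, in both arms, and name that score as the baseline for the primary outcome. In the CBT arm it then falls within about a week of treatment. State also whether T0 or T0.1 is the waiting-list arm's baseline in the within-group analysis.

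The cost is one short self-report form for about 30 people already in contact with the team, with no change in sample size. Repeating all ten questionnaires would be about 165 items (19 + 20 + 30 + 16 + 24 + 8 + 19 + 9 + 15 + 5), which is why the ICG alone is the minimum. The repeat removes the selection artefact and most of the pre-treatment gap in the CBT arm. It does not remove natural change during and after treatment.

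If T0 is already a separate assessment after screening, one sentence giving its timing is enough.
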